### Randomization

Based on research experience, only nursing homes with 150 beds or more have RNs on each unit to manage care services and to supervise PCAs. Moreover, there are two types of nursing.

homes: state-owned nursing homes and not-for-profit privately-owned nursing homes (the majority) and the former has a greater wealth of resources. The size of nursing homes and sources of funding are major characteristics that influence quality of care [26]. To minimize difference between the two groups, participating nursing homes will be grouped into four categories according to ownership and size, and modified stratification will be applied to the group assignment to improve the equivalence of the intervention group and the control group. Computer generated random numbers will be used for group assignment and this will be performed by an independent statistician (see Fig. 1).

**Fig. 1 Fig1:**
[figure not shown]
Randomization

### Description of the ACCM model intervention

This study has adapted the key characteristics of the Australian ACCM Model of Change described as the ‘Six Steps to Better Practice’ (see Fig. 2). The organizational structure of the ACCM Model is outlined in Fig. 3. The Steering Committee will be specifically established for this trial and will comprise the Principle Investigator, Co-Principle Investigators, Hunan Government representatives, representatives from the main project participants and representatives from the seven intervened nursing homes. Each nursing home will appoint a RN as a Clinical Mentor and each unit will appoint a RN or licensed nurse as a Site Champion.

**Fig. 2 Fig2:**
[figure not shown]
Six Steps to Better Practice (Morey et al., 2015, p.15–16)

**Fig. 3 Fig3:**
[figure not shown]
Organizational Structure of the ACCM Model

### Description of the ACCM model intervention

The intervention components, as described in the following section, will continue for 12 months. An evidence-based knowledge translation education program will be developed to enable the implementation of the ACCM model, and includes five modules: (i) Introduction to ACCM model; (ii) Leadership and clinical coaching in ACCM model; (iii) Urinary incontinence prevention; (iv) Pressure injury prevention and (v) falls prevention (see Table 2). The education program is based on the aim of the trial and the priorities in quality improvement identified by stakeholders in an industry consultation and a comprehensive literature search. The train-the-trainer method will be applied to implement the education program in which the Clinical Mentors will attend a 3-day intensive workshop (modules 1–5) and the Site Champions will attend a 2-day workshop (modules 2–5). The Clinical Mentor will work in collaboration with the Site Champions to implement the education program through education and training activities for staff. In each learning module, the project team will provide the Clinical Mentors and Site Champions with facilitator’s manuals and provide staff with a workbook to enhance interactive learning.

**Table 2 Tab2:** Structured and Evidence-Based Quality Improvement Education Program

Modules	Participants
Module 1. The strategies and procedures for the Aged Care Clinical Mentor to Create and Sustain Quality Improvement	ACCMs
Module 2. Effective leadership and clinical coaching for staff	ACCMs & Site Champions
Module 3. Evidence-based urinary incontinence management for residents	ACCMs & Site Champions
Module 4. Evidence-based pressure injury prevention for residents	ACCMs & Site Champions
Module 5. Evidence-based falls prevention	ACCMs & Site Champions

Note: ACCMs = Aged Care Clinical Mentors

The Clinical Mentors will develop an action plan every three months and discuss the action plan in the regular Steering Committee meetings in order to gain feedback from the Committee to revise or amend the plan. The Clinical Mentor will also receive regular written feedback based on the analysis of outcome measures on baseline data, and at 6 and 12 months post-intervention to foster quality improvement. An Academic Coach, who is an academic member of the University and is specialized in geriatric nursing, will be appointed to support Clinical Mentors to implement the action plan, monitor the process, and update standards, procedures, and in-service education based on the outcomes of the project. The Clinical Mentors and Site Champions will be given paid time of eight hours per week to deliver education modules and mentor staff to translate knowledge at the point of care.

### Description of control group

Nursing homes in the control group will receive routine training and information about the current care standards for residents that are applicable all nursing homes in Hunan Province. If they have further questions about the quality of care for the project team, they will be referred to relevant resources provided by the Hunan Provincial Civil Affairs Department that, again, are available to all nursing homes.

### Recruitment

Recruitment of nursing homes and care staff will be based on the selection criteria. A letter of invitation will be sent to all eligible nursing home managers to gain their informed consent to participate in the trial. Managers will administer confidentiality agreements regarding group assignment with the project team. However, the ACCM model will be introduced to all participating nursing homes after the trial.

### Outcome measures and data collection

#### Primary outcomes

Primary outcomes include: (i) Nursing homes’ capacity to create and sustain quality improvement; (ii) Staff perceptions of Person-centered Care; (iii) Self-reported quality of care by residents; and (iv) quality indicators that include falls, fall-related injuries, pressure ulcers and urinary incontinence at 12 months follow-up adjusted for baseline value.

#### Secondary outcomes

Secondary outcomes are the following outcomes adjusted for baseline value: (i) Residents’ quality of life; (ii) Residents’ unplanned admissions to acute care hospitals due to adverse events, as described in the primary outcomes; (iii) Self-reported quality of care by staff; (iv) Staff job satisfaction; (v) Staff intention to leave.

#### Instruments

The instruments and their relationship to outcomes and hypotheses are presented in Table 3 [12, 27–33].

**Table 3 Tab3:** Description of instruments used in outcome measures

Outcomes	Instruments description	Hypotheses
Nursing homes’ capacity to create and sustain quality improvement	Shortell’s Organization and Management Survey had been adapted to nursing home to evaluate nursing homes’ capacity to create and sustain quality improvement by Scott [27]. The scale has 35 items, consists of 5 subscales related to communication and leadership. Cronbach’s α of the Chinese version is 0.87 [27].	H_1_- nursing homes’ capacity to create and sustain evidence-based quality
Perceptions of quality of care	A single item on a 4-point Likert scale which is dichotomized as very low or rather low opposed to rather high or very high [12].	H_6_&H_3_ - perception of quality of care
Person-centered Care Assessment Tool	Person-centered Care Assessment Tool consists of three subscales: the extent of personalizing care, amount of organizational support, degree of environmental accessibility, Cronbach’s α of the Chinese version is 0.68 [28, 29].	H_2_- staff’s perceptions of Person-centered Care
Staff job satisfaction	Minnesota Satisfaction Questionnaire in short form has 20 items was used to examine satisfaction with professional life, Cronbach’s α of the Chinese version is 0.95 [30].	H_7_- job satisfaction
Staff intentions to leave	Turnover Intention Scale has 6 items and Items are scored using 4-point Likert. The Chinese version has been tested and used to assess the turnover intention of care staff. Cronbach’s α of the Chinese version is 0.92 [31].	H_8_- staff intention to leave
Residents’ quality of life	The12-item Short-Form Health Survey has 8 domains include Physical Functioning, Role-Physical, Bodily Pain, General Health, Vitality, Social Functioning, Role-Emotional, and Mental Health. Cronbach’s α of the Chinese version is 0.91 [32].	H_4_- residents’ quality of life
	Quality of Life in Late-Stage of Dementia has 3 factors and 11 items, with the factors being depressive mood, behavioral symptoms of discomfort, and positive behavioral signs of social interaction. Cronbach’s α of the Chinese version is 0.74 [33].	

#### Economic evaluation

Medical costs for each resident will be documented and collected in relation to treatment for fall-related injuries, new pressure ulcers, new urinary tract infections, and visits and readmissions to acute care hospitals. Cost-effectiveness will be expressed through a cost saving ratio and/or the outcomes per cost of intervention.

#### Data collection

The data will be collected before the intervention, and at 6 and 12 months after the commencement of intervention, for both intervention and control groups. A project manager will be appointed to coordinate the data collection process. Independent investigators who are blind to study assignment will distribute, collect and assist residents and staff to complete the survey. The Clinical Mentors in the intervention arm, and a liaison person in each control nursing home, will be tasked to work together with the project manager to complete the incident record form on falls, fall-related injuries, pressure ulcers and urinary tract infections on a weekly basis. The quality indicators will be carefully tracked by the following methods: (i) weekly follow-up and surveillance of the adverse events that will be recorded and submitted by the site managers; (ii) checking of residents’ progress notes and handover reports by research assistants to verify the incidents.

Each staff member and resident will be assigned a code number to protect their identity. This will also allow the researcher to re-identify them if needed. In order to be able to link all three surveys together without revealing staff identities, the project team will implement an identification method in which care staff members will be asked to write their maternal grandparents’ first names next to a unique site character on the front page of each survey.

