## Methods

### Study design

The ACCM model will be tested using a single-blind cluster randomized controlled trial (RCT) design. The study will be undertaken in Hunan Province, the seventh largest populated province in China, and home to 12.01 million people aged 60 or over where one-sixth of them were living with disabilities in 2015 [23]. Fourteen nursing homes in Hunan Province will be randomly selected and divided into two groups: the intervention group and the control group. Cluster RCT will be applied to the study to reduce influence from the interplay of subjects from the same nursing home. Because of the nature of the intervention, it is not possible to mask the study assignment from the research interventionists (the project team who will deliver the intervention), though staff at participating sites will be unaware of group assignment. The outcomes assessment will be performed by independent investigators who will be blinded to the group assignment. The standard protocol items named “Recommendations for Interventional Trials (SPIRIT)” that provides an overview of schedule of enrolment, interventions and assessments is presented in Table 1. The SPIRIT checklist is shown in Additional file 1.

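### Blinded outcome assessment is claimed for the whole trial, but three primary quality indicators are recorded by different roles in the two arms, in the intervention arm by the Clinical Mentors who deliver the program

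*Protocol article*

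**What the plan says.** Study design calls the trial single-blind and makes two blinding statements. On assessors: "The outcomes assessment will be performed by independent investigators who will be blinded to the group assignment". On staff: "though staff at participating sites will be unaware of group assignment". Neither is restricted to particular outcomes.

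Primary outcomes lists, as its fourth item, "quality indicators that include falls, fall-related injuries, pressure ulcers and urinary incontinence at 12 months follow-up adjusted for baseline value".

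Data collection gives the blinded investigators one task: to hand out, collect and help with the survey. The adverse events take another route: "The Clinical Mentors in the intervention arm, and a liaison person in each control nursing home, will be tasked to work together". The project manager joins them in this work, which is to "complete the incident record form on falls, fall-related injuries, pressure ulcers and urinary tract infections on a weekly basis". Site managers record and submit the events weekly, and research assistants check progress notes and handover reports to verify incidents. The article does not say whether these assistants are blinded.

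The Mentor's role is set out under Description of the ACCM model intervention: "The Clinical Mentor will work in collaboration with the Site Champions to implement the education program through education and training activities for staff". Mentors attend a 3-day workshop that includes the pressure injury and falls modules. Also, "The Clinical Mentor will also receive regular written feedback based on the analysis of outcome measures on baseline data", with further feedback at 6 and 12 months. Staff in intervention homes receive materials directly, since the project team will "provide staff with a workbook to enhance interactive learning". Mentors and Site Champions have eight paid hours a week for teaching and mentoring. Control homes receive routine training and information only.

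**The concern.** Falls, fall-related injuries and pressure ulcers are events that someone has to notice and write down. If the recorder in one arm is the person whose program is being judged, and the recorder in the other arm has a different role, an arm difference in recorded events mixes a difference in care with a difference in recording. The direction cannot be predicted. A Mentor newly trained in falls and pressure injury may notice more, or may be reluctant to report events that count against the program.

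The unqualified blinding statement would lead readers to trust these indicators as independently assessed. Likewise, the statement that staff are unaware of assignment would lead readers to treat staff ratings as blinded when the raters know that they are being taught and mentored under a new program.

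**Working it through.** The plan gives no figure on this point, so the check is a comparison of sections, followed by an illustration of size.

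**1. Who assesses what**

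| Outcome | Source or rater | Blinded according to the article? |
|---|---|---|
| Falls, fall-related injuries, pressure ulcers (primary) | Clinical Mentor (intervention) or liaison person (control), with the project manager; submitted by site managers; verified by research assistants | None of these roles is said to be blinded |
| Urinary incontinence (primary) | Not on the incident form, which lists urinary tract infections instead | Not stated |
| Staff perceptions of person-centered care, H2 (primary) | Staff self-report | Survey handlers blinded; the rater is the staff member |
| Capacity for quality improvement, H1 (primary) | Rater not named; probably staff, since the instrument is an organization and management survey | Survey handlers blinded |
| Quality of care, H3 (primary) | Residents (Primary outcomes) or residents or families (Hypotheses) | Survey handlers blinded |
| H6 to H8 (secondary) | Staff self-report | As for H2 |

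The general claim under Study design therefore does not cover the incident form. For self-reported outcomes the respondent is the assessor, so a blinded survey handler does not blind the outcome.

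**2. Who knows the arm**

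- Clinical Mentors deliver the program, so they know it.
- Site managers enter confidentiality agreements about group assignment (Recruitment), which implies that they know it.
- Research assistants work from notes and handover reports kept by the homes; nothing is said about masking.
- Staff in intervention homes receive a workbook, modules and mentoring; staff in control homes do not.

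**3. Whether baseline adjustment helps**

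The outcomes are adjusted for baseline value. The Mentors' training and the feedback they receive are part of the intervention and begin with it. A change in recording that they cause arises after baseline, and baseline adjustment cannot remove it.

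**4. Size, under an assumed range**

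The article gives no recording rates. Assume equal recording in both arms except for a proportion u under-recorded, or o over-recorded, in the intervention arm, each between 10% and 30%.

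Under-recording with no true effect: apparent rate ratio = 1 − u.

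- u = 0.10: 0.90
- u = 0.20: 0.80
- u = 0.30: 0.70

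Applied to the fall rate of 14.7% to 34% in the Background, the spurious reduction is rate × u:

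- u = 0.10: 1.5 to 3.4 percentage points
- u = 0.30: 4.4 to 10.2 percentage points

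Over-recording that hides a true effect: the apparent ratio is true ratio × (1 + o). Setting this to 1 gives true ratio = 1/(1 + o).

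- o = 0.10: 1/1.10 = 0.91
- o = 0.30: 1/1.30 = 0.77

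The two directions are not mirror images: 30% over-recording hides a ratio of 0.77, not 0.70.

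**The case against.** The recording system has safeguards. Both arms use one form, one weekly schedule and one project manager; site managers also submit events; and the check of notes is one of two stated tracking methods. A reader might infer that the Mentors are the only recorders. The text does not support that, and the 10% to 30% range is not an estimate of the error left after these steps. But no person in this chain is said to be blinded, and the role still differs by arm, so the safeguards lessen the problem without removing it.

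Other stronger readings are tempting and should not be made:

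- That the control liaison is untrained. The article says nothing about the liaison's training in completing the form; it only describes no program modules for control homes.
- That the chart check cannot find unreported events. The wording about verifying incidents is ambiguous on this.
- That all four indicators are affected. The form does not list urinary incontinence.
- That staff rate all the remaining primary outcomes. H3 is rated by residents or families, and the rater for H1 is unnamed.

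On staff blinding, the phrase could mean that staff are not told that there is a comparison or which arm they are in. Recruitment describes confidentiality agreements, and the Discussion says that mentoring will be fitted into existing training and supervision. It is therefore an inference, not a fact in the text, that staff will know their arm. The inference is strong, however, and knowing that one receives a new program is enough to influence self-report. Unblinded self-report is inherent in a staff education trial; this part calls for a corrected sentence, not a new design.

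Finally, the sample size rests on staff perceptions, not on these indicators. That limits how much of the trial depends on them, but they are still named as primary.

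**Conclusion.** The point holds. The statement that blinded independent investigators assess outcomes contradicts the article's own account of data collection for falls, fall-related injuries and pressure ulcers. For these three of the four primary quality indicators, recorder role is confounded with arm, and the recorder in the intervention arm delivers the program and receives outcome feedback. The bias can go either way and cannot be repaired in the analysis.

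Its size is unknown. Under the assumed 10% to 30%, it ranges from an apparent rate ratio of 0.90 to 0.70 with no effect, to the concealment of a true ratio of 0.91 to 0.77. These figures assume equal recording otherwise and no correction by the project manager, site managers or chart check.

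The statement that staff are unaware of assignment is not credible given what intervention staff receive. It bears on H2 (primary), on H6 to H8, and probably on H1.

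**What to change.** 1. Use the same recorder role in all 14 homes: a liaison person who is neither Clinical Mentor nor Site Champion, working with the project manager as already planned.
2. Have the research assistants make the planned check of notes and handover reports by the same procedure in both arms, without knowledge of arm as far as feasible, and count events found in the notes that were not submitted.
3. Under Study design, limit the claim of blinded assessment to survey administration, drop the claim that staff are unaware of assignment, and describe staff-reported outcomes as unblinded self-report.

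The cost is a form reassigned in seven homes, somewhat more work in a check that is already planned, and a less favourable blinding statement. A full weekly search of all records is not asked for: with 14 homes of at least 150 beds (14 × 150 = 2,100 beds or more) it would be a substantial extra workload. Some differential recording may remain, because the liaison is still site staff in a home that runs the program and the notes may reveal the arm.

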**Methods:**

A cluster randomized controlled trial will be applied to the study. Fourteen nursing homes will be randomly allocated to either the intervention group (*n* = 7) or the control group (*n* = 7). Forty staff will be recruited from each nursing home and the estimated sample size will be 280 staff in each group. The intervention includes a structured, evidence-based quality improvement education program for staff to facilitate knowledge translation in evidence-based quality improvement targeting urinary incontinence, pressure injury and falls prevention. The primary outcomes are nursing homes’ capacity to create and sustain quality improvement, staff perceptions of person-centered care, self-reported quality of care by residents and selected quality indicators at 12 months follow-up adjusted for baseline value. Secondary outcomes are residents’ quality of life, residents’ unplanned admissions to acute care hospitals, quality of care reported by staff, staff job satisfaction and staff intention to leave adjusted for baseline value. A mixed linear regression model will be adopted to compare the significant differences between groups over a 12-month period.

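### Urinary incontinence is a primary quality indicator, but the weekly incident form lists urinary tract infection in its place, and no data source for incontinence is described

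*Protocol article*

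**What the plan says.** Primary outcomes (Protocol article) gives the fourth primary outcome as "quality indicators that include falls, fall-related injuries, pressure ulcers and urinary incontinence at 12 months follow-up adjusted for baseline value". The abstract describes the intervention as "evidence-based quality improvement targeting urinary incontinence, pressure injury and falls prevention", and one of the three clinical education modules deals with incontinence, so its place among the outcomes looks intended.

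Data collection describes the capture. The Clinical Mentors in the intervention homes and a liaison person in each control home are to "complete the incident record form on falls, fall-related injuries, pressure ulcers and urinary tract infections on a weekly basis". The indicators are then followed in two ways: "weekly follow-up and surveillance of the adverse events that will be recorded and submitted by the site managers", and "checking of residents’ progress notes and handover reports by research assistants to verify the incidents".

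Two other sections touch the same list. Economic evaluation costs "treatment for fall-related injuries, new pressure ulcers, new urinary tract infections, and visits and readmissions to acute care hospitals". Secondary outcomes includes "Residents’ unplanned admissions to acute care hospitals due to adverse events, as described in the primary outcomes".

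**The concern.** The outcome list and the recording form carry the same first three items and a different fourth. Sites that follow Data collection as written would return infection counts, and the described data would hold no incontinence value at baseline or at 12 months. The indicator would then go unmeasured, or an analyst would have to choose a substitute after the fact. In either case the trial could not show whether its incontinence module changed what it was meant to change. A baseline status that was not recorded at the time may not be recoverable later. The admissions outcome defines its qualifying events by pointing back to the primary list, so it inherits the doubt.

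**Working it through.** The check is a comparison of text. The protocol states no figure on this point to reproduce.

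**Step 1. Match the indicators to the form.**

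| Primary quality indicator | On the weekly incident form? |
|---|---|
| Falls | Yes |
| Fall-related injuries | Yes |
| Pressure ulcers | Yes |
| Urinary incontinence | No; urinary tract infection is listed instead |

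Three of the four match. The one extra item on the form, urinary tract infection, is not itself named as a primary or secondary outcome.

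**Step 2. Look for another source.** The first tracking method covers adverse events that sites have recorded. The second has research assistants check notes to confirm incidents, which verifies existing entries and does not establish each resident's status. Neither names incontinence. Table 3 lists questionnaires only. It also has no entry for falls or pressure ulcers, so its silence on incontinence proves nothing either way.

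**Step 3. Ask whether adding incontinence to the form would be enough.** Inputs: prevalence of about 65.8% (Background) and the minimum home size of 150 beds (Inclusion and exclusion criteria). Full occupancy is assumed.

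- Residents already incontinent in one such home: 150 × 0.658 = 98.7, about 99.
- Residents who could still have a first onset: 150 − 98.7 = 51.3, about 51.
- Already incontinent across 14 such homes: 98.7 × 14 = 1,381.8, about 1,380.

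A form for new incidents would say little about the larger group, in whom any benefit would show as improvement or resolution. A 12-month value adjusted for baseline needs a status at both times.

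**Step 4. Size the extra recording.** On the same assumptions, 150 × 14 = 2,100 residents per time point, and 2,100 × 3 = 6,300 status records over the three collections. These headcounts show scale only. They do not measure bias or loss of power.

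**The case against.** A reader might infer that incontinence will certainly have no data. The documents do not support that. Data collection says in general terms that the quality indicators will be tracked. The Background and Secondary outcomes both use the term adverse events in a sense that can include incontinence. The assessment schedule (Table 1) and the supplementary file are not shown. What stands is narrower: no record or definition for incontinence is described, and the one explicit list of recorded items conflicts with the outcome list. That is a conflict between two stated lists, so the fact that an article condenses a fuller protocol does not explain it.

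A reader might also take Economic evaluation as a second contradiction, because it too names urinary tract infection. It is not one. It lists treatment costs, and costing infections is compatible with measuring incontinence. Nor does the text say that infection counts will replace incontinence in the analysis; that is only a risk.

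On weight, it is fair to note that none of hypotheses H1 to H8 concerns the quality indicators and that the sample size rests on a staff measure. H1 to H3 are untouched. This limits the reach of the problem, but incontinence remains a named primary outcome.

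**Conclusion.** The inconsistency is real and should be corrected before main-study baseline. It affects one of four components of one of four primary outcomes and carries over to the events that define the admissions outcome. The conclusion rests on the wording of Primary outcomes and Data collection, and on the plain fact that incontinence and urinary tract infection are different conditions. It needs no numerical assumption. The prevalence bears only on the further point that an incident form suits incontinence poorly, and it is an approximate background figure. If Table 1 does list incontinence, a source may exist, but the two sections would still need to be brought into agreement.

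**What to change.** Reconcile Primary outcomes and Data collection. The preferred route is as follows:

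- Record each resident's continence status at the existing baseline, 6- and 12-month collections, using one written definition and the same source in both arms.
- Have it recorded by assessors blinded to allocation, as Study design requires of outcome assessment. Data collection does not describe the research assistants who check notes as blinded, and their stated task is to verify incidents, so the protocol should say who does this work.
- Analyse 12-month prevalence adjusted for baseline.

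If incontinence is not to be measured, correct the named indicator instead. Urinary tract infection can stay as a cost item in Economic evaluation. The admissions outcome should refer to the reconciled list.

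The cost is a wording change plus one status record per resident at three time points, about 2,100 per time point on the assumptions above. That is more than a single added line on a form, but it uses collections already planned. Trial status describes only the pilot as begun, so on the article's timeline there is still room to make the change before main-study baseline.
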